**Methods/design:**

We will conduct a two-arm randomized controlled trial (RCT), along with a follow-up qualitative process study to explore the findings in greater depth. All CBOs affiliated with Canadian AIDS Society (n = 120) will be invited to participate and will be randomized to receive either the 'full-serve' version of SHARE or the 'self-serve' version (a listing of relevant systematic reviews with links to records on PubMed and worksheets that help CBOs find and use research evidence) using a simple randomized design. All management and staff from each organization will be provided access to the version of SHARE that their organization is allocated to. The trial duration will be 10 months (two-month baseline period, six-month intervention period, and two month crossover period), the primary outcome measure will be the mean number of logins/month/organization (averaged across the number of users from each organization) between baseline and the end of the intervention period. The secondary outcome will be intention to use research evidence as measured by a survey administered to one key decision maker from each organization. For the qualitative study, one key organizational decision maker from 15 organizations in each trial arm (n = 30) will be purposively sampled. One-on-one semi-structured interviews will be conducted by telephone on their views about and their experiences with the evidence service they received, how helpful it was in their work, why it was helpful (or not helpful), what aspects were most and least helpful and why, and recommendations for next steps.

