## Objectives

Our objective is to evaluate whether, how, and why this 'full serve' evidence service increases the use research evidence by key decision makers in CBOs as compared to a 'self-serve' evidence service.

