## Methods/design

We will conduct this trial using a sequential explanatory mixed methods design [25], beginning with the two-arm randomized controlled trial (RCT), and then following up with a qualitative process study to explore the RCT findings in greater depth. The trial will run for 10 months, which includes a two-month baseline period where all participants receive the 'self-serve' evidence service, a six-month period where the intervention group will receive the 'full-serve' evidence service and the control group will continue to receive the 'self-serve' evidence service, and a final two-month period where both groups will receive the 'full-serve' version of SHARE.

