### Outcomes

Measuring the impact of knowledge transfer and exchange (KTE) interventions, such as the evidence service proposed here, poses significant challenges as there is a long chain of factors between a KTE intervention such as SHARE and the health status of clients of CBOs or of broader populations [10,35]. For example, it has been demonstrated that assessing the impact of KTE interventions on the practice of physicians poses challenges due to the fact that many factors other than the practice guidelines or recommendations that were disseminated may influence how practices are changed [36-38].

Given these constraints, our primary and secondary outcomes for the trial are proxy measures for research use. The primary outcome will be a measure of utilization that is similar to what Haynes *et al*. (2006) used in their trial of the McMaster Premium Literature Updating Service (PLUS) [39]. Specifically, we will track utilization at the organizational level by calculating the mean number of logins/month/organization (the total organizational logins/month will be averaged across the number of users from each organization) across trial groups during each of the baseline period, intervention period, and crossover period. We will also provide related descriptive measures such as the mean number of logins/month for different types of positions within the organization (executive director, management and staff), the range of logins/month within the organization, the proportion of organizations with at least one user accessing the 'full serve' and 'self-serve' versions of SHARE each month, the frequency with which systematic review records and related resources are accessed (*e.g.*, URLs to abstracts, user-friendly summaries, and/or full-text), and the number of times the email updates to the 'full-serve' group are forwarded.

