### Data management and analysis

Data will be entered into SPSS 16.0 using unique identifiers that link each participant to their respective organizational identifier assigned during the randomization process. Analyses will be conducted by two members of the team ([name] and TB) and, during the analysis, all investigators -- except for one of us who is involved in the both the analysis and randomization (TB) -- will be blinded to the key linking the organizations to their unique identifiers.

We will treat both outcome measures as continuous variables and analyze the change in these measures over time using a two-way mixed effects linear repeated measures analysis of variance (ANOVA), which will assess the effects within groups, between groups, and over time with the latter as the main feature of interest. In addition, we will control for four variables -- province the organization is located in, size of organization (as measured by number full-time equivalent staff in the organization), number of participants that participated from each organization, and the number of clients served each year by the organization -- using analysis of covariance. For the analysis of the secondary outcome, we will also control for whether the key decision maker is full-time or part-time, and whether they have had research training in the past. Each of these variables may at least partially explain research use (*e.g.*, the amount of staff support an executive director or manager has may determine the extent to which they can spend time finding and using research evidence), and therefore adjusting for them will allow for a better assessment of the effects of the intervention. Moreover, as part of a secondary analysis, we will assess whether there is an interaction between each (entered as fixed factors) and the outcome measures. Given the likelihood that the distribution of the outcomes will be skewed, we will transform the data where necessary and possible, which may include adjusting the time period for which we calculate the mean number of logins/month/organization (*e.g.*, calculating the mean over two months) if the number of logins is low and there are insufficient data for analysis. We will also qualitatively compare the number of participants in the intervention and control groups that do not complete the follow-up survey, and attempt to assess if there are reasons for why they dropped out based on their baseline characteristics.

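### The analysis section makes the effect over time its chief interest and names no between-arm test with a fixed window, so as written it tests something other than the six-month arm difference on which precision was calculated

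*Protocol article*

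**What the plan says.** The objective is comparative: whether full-serve "increases the use research evidence by key decision makers in CBOs as compared to a 'self-serve' evidence service". For both outcomes, the plan in Data management and analysis is to "analyze the change in these measures over time using a two-way mixed effects linear repeated measures analysis of variance (ANOVA"). The same sentence then sets out what this model is for and where its priority lies: "which will assess the effects within groups, between groups, and over time with the latter as the main feature of interest". The only interactions mentioned there are secondary ones involving the four organizational covariates. The section does not say which months enter the model.

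Three other places bear on the window:

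- **Abstract, Methods/design:** the primary outcome is mean logins per month per organization "between baseline and the end of the intervention period".
- **Outcomes:** logins are calculated "across trial groups during each of the baseline period, intervention period, and crossover period".
- **Statistical precision:** detectable differences are for the time-averaged contrast between the two groups, from six monthly points in the intervention period.

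The Methods/design section describes "a two-month baseline period where all participants receive the 'self-serve' evidence service" and "a final two-month period where both groups will receive the 'full-serve' version of SHARE". The arms therefore receive the same service in four of the ten months.

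**The concern.** In a two-way ANOVA with factors group and time, the time main effect asks whether the average over both arms changes. It can be significant because logins fall everywhere as novelty fades, or rise everywhere as users settle in, with no difference between services. The randomised comparison lies in the group-by-time term or in a between-group contrast over the intervention months. The text singles out neither.

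Taken at its word, the plan could report a shared trend as its main finding. Anyone who sees the problem must depart from the text, and the text does not say to which test: a between-groups main effect over some set of months, a group-by-month test, a group-by-period contrast, or the six-month difference used for precision. These have different power, and the choice would then be open after the data are seen.

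**Working it through.** **Inputs from the article.** Statistical precision gives 42 organizations per arm, SD 1.0, two-sided 0.05, 80% power, six monthly points, and ICCs over time from 0.2 to 0.8. Methods/design gives 2 baseline, 6 intervention and 2 crossover months.

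**Assumptions added here.** Compound symmetry with correlation ρ; a constant service effect d in the six intervention months and none in the others; where stated, a shift s common to both arms after baseline. Below, 2.80 = 1.96 + 0.84, and triplets are for ICC 0.2 / 0.5 / 0.8 unless noted.

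**1. The article's own figures.** d = 2.80 × sqrt(2(1 + 5ρ)/(42 × 6)). At ρ = 0.5 this is 2.80 × sqrt(7/252) = 0.467. For ICC 0.2, 0.3, 0.5, 0.7 and 0.8 it gives 0.353, 0.395, 0.467, 0.529 and 0.558, against the stated 0.35, 0.39, 0.47, 0.53 and 0.56. The figures reproduce, so precision rests on a between-group mean over six months, not on an effect over time.

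**2. The literal test: time main effect, no service effect.** Over eight months (2 + 6) with month as a factor there are 7 and 82 × 7 = 574 df, and the noncentrality is 84 × s² × (2 × 6/8)/(1 − ρ).

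| Common shift s | Noncentrality | Probability significant |
|---|---|---|
| 0.3 SD | 14.2 / 22.7 / 56.7 | 79% / 96% / >99% |
| 0.2 SD | 6.3 / 10.1 / 25.2 | 39% / 61% / 97% |
| 0.1 SD | 1.6 / 2.5 / 6.3 | 12% / 16% / 39% |

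A one-df contrast of intervention with baseline has SE sqrt((1 − ρ)(1/2 + 1/6)/84) = 0.080 / 0.063 / 0.040. At s = 0.3 it is significant with probability 96% / >99% / >99%. A simulation of the monthly ANOVA at ICC 0.5 and s = 0.3 (3,000 runs) gave about 95% for time, while the group and group-by-time tests stayed near 5%.

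**3. The between-groups main effect, with d from step 1.**

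- *Eight months:* the effect shrinks to (6/8)d and the SE is sqrt(2(1 + 7ρ)/(42 × 8)). At ρ = 0.5: 0.350/0.164 = 2.14, and Φ(2.14 − 1.96) = 57%. Power is 60% / 57% / 56%.
- *Ten months, no arm difference in crossover:* the effect is (6/10)d and the SE is sqrt(2(1 + 9ρ)/(42 × 10)). At ρ = 0.5: 0.280/0.162 = 1.73, and Φ(1.73 − 1.96) = 41%. Power is about 45% / 41% / 40%.

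**4. Contrasts that do target the question.**

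- *One-df group by period, intervention minus baseline:* the detectable difference is 2.80 × sqrt(2(1 − ρ)(1/2 + 1/6)/42) = 0.45 / 0.35 / 0.22.
- *Intervention mean adjusted for baseline mean:* the residual variance is (1 + 5ρ)/6 − ρ²/((1 + ρ)/2) = 0.267 / 0.250 / 0.122, and 2.80 × sqrt(2 × variance/42) = 0.32 / 0.31 / 0.21.

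The published 0.35 / 0.47 / 0.56 rises with ICC. The group-by-period figure falls with ICC. Precision as printed is therefore not the precision of a group-by-time analysis.

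**The case against.** The best defence is that the wording is loose but the intent is plain. The analysis is of change over time in a two-way model, the objective compares two services, and precision is given for a difference between groups. A pooled time test fits none of these, so over time is naturally read as change over time by group. If time has two levels, baseline and intervention, group by time is already a one-df contrast of the right kind. The same sentence also plans a between-groups effect.

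Much of this stands. Group by time may well be what was meant, and the model can supply it. A reader might infer that the stated analysis cannot answer the trial's question; that goes too far. What remains is that between groups is a separate item in the list, the item given priority is the other one, and no sentence names the interaction. Even on the favourable reading, the number of time levels is open. At ICC 0.5 and a difference of 0.47 SD, a seven-df group-by-month test has about 77% power and the one-df group-by-period contrast about 96%.

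A reader might also infer from the Outcomes section that the crossover months belong in the primary test. No section says so. The abstract stops at the end of the intervention, precision uses six months, and Outcomes may only be describing a per-period summary. The survey outcome is not measured in the crossover at all. The fair statement is that Outcomes and the analysis section do not exclude those months. The eight-month dilution in step 3 does not depend on them.

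**Conclusion.** The point holds as a mismatch within the article. The effect given priority in the analysis section is not, as written, a comparison of the randomised arms, and it is not the contrast on which precision was calculated. Three sections give three windows for the primary outcome.

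The consequence is material under the stated assumptions. A literal time test would usually be significant under a 0.3 SD common shift with no service effect, and seldom under 0.1 SD unless the ICC is high. The size of any shift is assumed, since the article gives none. Falling back on the between-groups main effect costs about 20 to 24 percentage points of power over eight months. The ten-month loss, to about 40% to 45%, applies only if the crossover months were averaged in and the arms did not differ there. The documents do not support saying that those months are in the primary test or that the model is unable to answer the question.

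**What to change.** State one primary test: the between-arm difference in mean logins per user per month over the six intervention months (trial months 3 to 8), adjusted for the organization's mean over the two baseline months. A one-df group-by-period contrast serves the same purpose. Whether baseline enters as a covariate or through constrained baseline means can be left to the statistician.

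State that months 9 and 10 lie outside this test and are reported separately. Label the time main effect and the within-arm changes as descriptive. Then use the same contrast and window in the abstract, Outcomes, Data management and analysis, and Statistical precision. With baseline adjustment, the detectable differences to print would be about 0.32 / 0.31 / 0.21 SD at ICC 0.2 / 0.5 / 0.8, under compound symmetry.

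The cost is a change of wording and a recalculated precision paragraph. No new data or design change is needed.

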For all analyses, we will use the intention to treat principle, report 95% confidence intervals, and consider p-values equal to or less than 0.05 (two-tailed) to be significant. For the primary outcome measure (mean logins/month/organization), missing data are irrelevant as they are a naturalistic measure. For the secondary outcome measure (obtained through the survey), missing data can be taken into account through the use of a mixed-effects model.

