### Statistical precision

Given a fixed sample size of approximately 85 organizations (70% of 120 organizations) a sample size calculation is not relevant. Instead, we have calculated the level of statistical precision that we can expect given our fixed sample size. To calculate the expected statistical precision in the trial, an estimation of intra-class correlation coefficient (ICC) of measurements for individuals over time for the primary outcome is required. However, we have no mechanism to estimate the ICC due to the fact that no similar study with this population has been conducted (at least to our knowledge). Therefore, we calculated estimates of statistical precision for ICCs of 0.2, 0.3, 0.5, 0.7 and 0.8 based on a six-month trial period with 80% power, an estimated standard deviation of 1.0, significance of 0.05 (two-sided test), and 42 organizations per study group (total n = 85) [50]. Assuming the primary outcome data will be collected from all 85 organizations during the intervention period at six follow-up points (one per month), the time-averaged detectible differences (in standard deviation units) between the two groups is at best 0.35 (for ICC = 0.2), which increases with successively greater ICCs to 0.39 (for ICC = 0.3), 0.47 (for ICC = 0.5), 0.53 (for ICC = 0.7), and 0.56 (for ICC = 0.8).

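### The analysis section makes the effect over time its main interest, which read as written pools both arms; no between-arm contrast is named as the primary test

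*Protocol article*

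**What the plan says.** All places are in the protocol article.

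- **Objectives.** The question is comparative: whether full-serve "increases the use research evidence by key decision makers in CBOs as compared to a 'self-serve' evidence service".
- **Methods/design.** There is "a two-month baseline period where all participants receive the 'self-serve' evidence service". Six months follow in which the arms differ, then two months in which both arms have full-serve.
- **Primary outcome.** The abstract takes mean logins per month per organization "between baseline and the end of the intervention period". The Outcomes section tracks them "across trial groups during each of the baseline period, intervention period, and crossover period".
- **Data management and analysis (RCT).** Both outcomes are treated as continuous and put through a single model, a two-way mixed effects ANOVA for repeated measures applied to change. The same sentence then lists the effects that this model yields and ranks them: "which will assess the effects within groups, between groups, and over time with the latter as the main feature of interest". The only interactions mentioned there involve the covariates, as a secondary analysis. For all analyses the team will "consider p-values equal to or less than 0.05 (two-tailed) to be significant".
- **Statistical precision.** The figures given are "time-averaged detectible differences (in standard deviation units) between the two groups", for six monthly points in the intervention period: 0.35, 0.39, 0.47, 0.53 and 0.56 SD at ICCs of 0.2, 0.3, 0.5, 0.7 and 0.8.

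**The concern.** In a model with arm and time as its two factors, the effect of time is the change averaged over both arms. It carries no information on full-serve versus self-serve. Of the three effects listed, this is the one the sentence puts first.

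A shared trend is plausible. The database is new and not yet public, and every organization starts on the same service at the same moment, so logins could fall (or rise) in both arms after the first two months. A test of time would pick that up whatever the intervention does. It could also miss a real effect if a shared decline offset it.

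The significance rule covers all analyses and so does not settle which effect decides the trial. With the deciding contrast unnamed, the choice among time, arm, within-arm change and arm difference in change could be made after the data are seen.

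**Working it through.** **Inputs.** From the Statistical precision section: n = 42 per arm, SD 1.0, two-sided 0.05, 80% power, m = 6 monthly points, ICC (r) from 0.2 to 0.8. From Methods/design: 2 baseline and 6 intervention months. Assumed here: equal correlation between months, and a shared shift of 0.2 SD from baseline to intervention months. The multiplier is 1.960 + 0.842 = 2.802.

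**1. The plan's own figures.** Time-averaged arm difference over the six intervention months: 2.802 × √[2(1 + 5r)/(6 × 42)].

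| ICC | 0.2 | 0.3 | 0.5 | 0.7 | 0.8 |
|---|---|---|---|---|---|
| Stated | 0.35 | 0.39 | 0.47 | 0.53 | 0.56 |
| Recomputed | 0.353 | 0.395 | 0.467 | 0.529 | 0.558 |

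The figures reproduce. They belong to a between-arm comparison over months 3 to 8, not to an effect of time.

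**2. The time effect under a shared shift and no arm difference.** For two periods, SE = √[(1 − r)(1/2 + 1/6)/84], and power is Φ(0.2/SE − 1.96).

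- r = 0.2: SE = 0.0797, ratio 2.51, significant in 71% of trials.
- r = 0.5: SE = 0.0630, ratio 3.17, significant in 89%.
- r = 0.8: SE = 0.0398, ratio 5.02, significant in 99.9%.

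If time enters as eight monthly levels, the test has 7 degrees of freedom. The non-centrality is the ratio squared (6.3, 10.1, 25.2), and the percentages fall to about 40, 62 and 98. The size depends on how time is coded; the direction does not.

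**3. Simulation** (4,000 trials per setting, r = 0.5 assumed, 2 + 6 months).

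- Shared shift of 0.25 SD, no arm difference: time effect significant in 97%; arm effect and arm difference in change both near 5%.
- True arm effect of 0.47 SD with an offsetting shared trend of −0.235 SD: time effect significant in 5%, arm difference in change in 96%.

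**4. Two candidate between-arm contrasts.**

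- *Change score* (mean of six intervention months minus mean of two baseline months): detectable difference 2.802 × √[2(1 − r)(2/3)/42].
- *Intervention-period mean adjusted for the baseline mean*: the six-month mean has variance (1 + 5r)/6, the two-month mean (1 + r)/2, and their covariance is r. The residual variance is V = (1 + 5r)/6 − 2r²/(1 + r), and the detectable difference is 2.802 × √(2V/42).

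| ICC | Stated | Change score | Adjusted for baseline |
|---|---|---|---|
| 0.2 | 0.35 | 0.45 | 0.32 (V = 0.267) |
| 0.5 | 0.47 | 0.35 | 0.31 (V = 0.250) |
| 0.8 | 0.56 | 0.22 | 0.21 (V = 0.122) |

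At an ICC of 0.2 the change score has only about 60% power for the stated difference. The adjusted contrast does at least as well as stated at all three ICCs.

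**The case against.** The strongest reply is that one loose word is being read in isolation. The sentence opens by analysing change over time in a model that has arm as a factor. The objective, the outcome definition, the reason given for covariate adjustment and the precision figures all point to a comparison of arms. A condensed article may also leave the exact contrast to a fuller plan. Most of this stands: a difference in change between arms, loosely worded, is the likelier intent.

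It does not dispose of the point. The article is not silent; it ranks the effects and puts first one that does not compare the arms. No section names arm-by-time, a difference in change or an intervention-period arm difference as the primary test.

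Two stronger readings are tempting, and the documents do not support them.

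- A reader might infer that none of the effects listed is a treatment effect. That is wrong: the between-group effect over the six intervention months is a valid one, and the precision section uses it. It is diluted only if baseline or crossover months are averaged in, which no section says will be done.
- A reader might infer that a shared trend would be reported as evidence for the service. No section says so; that follows only from the literal reading of one clause.

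**Conclusion.** The point holds as a wrongly stated priority, not as proof that the trial would test the wrong thing. Read as written, the main effect does not answer the objective and does not match the contrast behind the precision figures. The size is 71% (ICC 0.2) or 89% (ICC 0.5) significant time effects with no arm difference. This rests on an assumed shared shift of 0.2 SD, a two-period test, equal correlation between months and 42 organizations per arm. With eight monthly levels the same shift gives about 40% and 62%. The documents give no estimate of a shared trend, so these figures are illustrative. The mismatch between the two sections does not depend on them.

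**What to change.** Replace the clause on the main feature of interest with one pre-specified contrast, for example:

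> The primary test is the full-serve minus self-serve difference in mean logins per month per organization over the six intervention months, adjusted for the organization's baseline-period mean, with its 95% confidence interval. Baseline and crossover months do not enter the averaged outcome. The time effect, the overall arm effect and within-arm changes are descriptive.

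For the intention outcome, test the between-arm difference at follow-up adjusted for the baseline score. The planned covariates can stay.

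This keeps the contrast of the Statistical precision section, whose figures remain valid as conservative values. They may be updated to about 0.32, 0.31 and 0.21 SD at ICCs of 0.2, 0.5 and 0.8. A change-score contrast would also compare the arms, but it would make those figures inapplicable and needs 0.45 SD at an ICC of 0.2. The cost is one or two sentences and an optional update of the precision figures, with no new data.

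### The p ≤ 0.05 significance rule is written for every analysis, so it also covers eight to ten covariate interaction tests that should be labelled exploratory

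*Protocol article*

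**What the plan says.** The Protocol article names one outcome of each rank. In the abstract (Methods/design), "the primary outcome measure will be the mean number of logins/month/organization", and "The secondary outcome will be intention to use research evidence as measured by a survey administered to one key decision maker from each organization". The Outcomes section keeps this ranking but describes the two together: "our primary and secondary outcomes for the trial are proxy measures for research use".

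The RCT section on data management and analysis then sets out the covariates. For both outcomes, "In addition, we will control for four variables": province, organization size, number of participants from the organization, and clients served per year. Two more are added for intention, namely working hours and earlier training in research: "For the analysis of the secondary outcome, we will also control for whether the key decision maker is full-time or part-time, and whether they have". The section continues: "Moreover, as part of a secondary analysis, we will assess whether there is an interaction between each (entered as fixed factors) and the outcome measures".

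The section closes with a two-tailed threshold of unrestricted scope: "For all analyses, we will use the intention to treat principle, report 95% confidence intervals, and consider p-values equal to or less than 0.05". It exempts no analysis from that threshold. The article nowhere calls the interaction analyses exploratory or adjusts for their number.

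**The concern.** This is a stated rule, not a detail left to a later analysis plan. An analysis plan that withheld or adjusted significance for the interactions would depart from the published text.

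Followed literally, the rule gives an interaction between study arm and, say, organization size or research training the same standing as the login comparison: p ≤ 0.05 and it is significant. With about 85 organizations and eight to ten such tests, a statement about which organizations benefit could arise by chance far more often than the 5% the rule suggests.

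A smaller matter concerns intention. Both outcomes are described as proxies for research use and both are judged by the same threshold. The text does not say how a significant intention result is to be read if logins show no difference.

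**Working it through.** **1. The plan's own figures.** The article states no error rate for the set of tests. Its only related figures are the detectable differences under Statistical precision, which use two-sided α = 0.05, 80% power, SD 1.0, 42 organizations per group and six monthly measurements. With m = 6 and n = 42,

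d = √[ 2 (1.960 + 0.842)² (1 + (m − 1)·ICC) / (m·n) ].

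For ICC = 0.2: √(2 × 7.849 × 2 / 252) = 0.353.

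| ICC | Stated | Recomputed |
|---|---|---|
| 0.2 | 0.35 | 0.353 |
| 0.3 | 0.39 | 0.395 |
| 0.5 | 0.47 | 0.467 |
| 0.7 | 0.53 | 0.529 |
| 0.8 | 0.56 | 0.558 |

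The figures agree to within rounding or truncation. The precision statement thus rests on a single unadjusted two-sided 0.05 test of the primary outcome, and it is sound on that point.

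**2. Counting the interaction tests.** Logins have four covariates. Intention has the same four plus two, so six. If each covariate is tested once per outcome, 4 + 6 = 10. If the interaction sentence refers only to the four shared covariates, 4 + 4 = 8. A covariate with several levels, such as province, is counted as one overall test; testing its levels separately would raise the count.

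**3. Chance of at least one false declaration.** With no true interactions and k independent tests at 0.05, the chance is 1 − 0.95^k:

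- k = 10: 1 − 0.95¹⁰ = 0.401
- k = 8: 1 − 0.95⁸ = 0.337

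Positive correlation between the tests lowers this. The documents give no correlation, so a range is shown. A simulation of 400,000 sets of ten equally correlated standard normal statistics, with a two-sided 1.96 cut-off, gave:

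| Common correlation | Ten tests |
|---|---|
| 0 | 0.40 |
| 0.3 | 0.35 |
| 0.5 | 0.29 |
| 0.8 | 0.17 |

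Even the lowest value is more than three times 0.05 (0.17 / 0.05 = 3.4); the highest is eight times.

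**4. The two main outcome tests.** The login test taken alone has an error of 0.05, however many other tests are run. If a reader accepted either outcome as proof of benefit, the chance of at least one false positive would be 1 − 0.95² = 0.0975 if independent, and 0.079 at a correlation of 0.8. That is a modest excess, and it arises only if the ranking of the outcomes is ignored.

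**5. Precision of an interaction on logins.** For a two-level covariate that splits the sample evenly (an assumption), the standard error of an interaction is twice that of the main effect. The stated detectable differences of 0.35 to 0.56 SD then become 2 × 0.35 = 0.70 to 2 × 0.56 = 1.12 SD. Only large interactions could be detected reliably, so a nominally significant one deserves caution.

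**The case against.** The strongest reply is that the plan already has a ranking. It names one primary outcome and one secondary outcome, places the interactions under a secondary analysis, and calculates precision for the primary outcome only. A shared threshold does not cancel that ranking. This stands. A reader might infer from the all-analyses wording that the trial has no hierarchy, or that its answer on whether the service works carries an inflated error. The documents support neither: the designated test is the one on logins, and it keeps its 5%. A false interaction is not a false primary finding.

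A reader might also infer from the figures that a false finding somewhere is likely. It is not. Adding both main outcome tests to the ten interactions gives 1 − 0.95¹² = 0.46 under independence, still below one half, and correlation lowers it. One half is passed only from 14 independent tests.

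It is also fair to say that no section plans a subgroup claim or says that intention may stand in for logins; these are possible uses of the rule, not stated intentions. The count depends on how a loosely worded sentence is read. And statisticians differ on whether a single named secondary outcome must be formally tested only after the primary succeeds.

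Finally, multiplicity rules for lower-ranked analyses are commonly left to an analysis plan. That would answer a complaint that the article is silent. It does not answer this one, because the article is not silent: it sets a significance threshold for every analysis, and the secondary label takes no interaction test out of it.

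**Conclusion.** The point holds in a limited form. The stated rule is too broad because it allows unadjusted declarations of significance for eight to ten interaction tests. With no true interactions, the chance of at least one false declaration among ten is about 0.17 to 0.40 for common correlations from 0.8 down to 0; for eight independent tests it is 0.34.

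This assumes one test per covariate and outcome, reads the interaction sentence as covariate by study arm, and uses equal correlation as a simple stand-in for an unknown structure. The primary test and the precision statement are unaffected. Severity is minor: a cheap improvement that guards against over-reading results on which organizations benefit.

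**What to change.** Two changes of wording in the RCT section on data management and analysis, made before results are known:

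- **Threshold sentence.** Limit the confirmatory two-sided 0.05 rule to the primary between-group test on logins. State that the intention result is supportive, is reported with its estimate and 95% confidence interval, and cannot replace a null login result.
- **Interaction sentence.** Label these analyses exploratory and report each as an estimate with a 95% confidence interval, without declaring significance. If a claim is wanted, list the tests and apply a Holm adjustment over them; with ten tests the smallest p-value is then compared with 0.05 / 10 = 0.005.

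Data collection, sample size and the primary test do not change. The cost is that the trial gives up unadjusted subgroup significance claims, and intention can no longer carry a positive conclusion by itself.
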